# STUDY SYNOPSIS

| **Project Leader** | [name]. [name]  Clinica Luganese Moncucco  [name]  [contact]  email: [contact] |
| --- | --- |
| **Study Title** | Tracheal etCO2 level and gastric pH level measurements as markers to confirm during the correct naso-gastric tube placement in unconscious patients. A physiological, prospective, observational study |
| **Study ID** | CLM_ICU_001 |
| **Protocol Version and Date** | Version 2, 31 Dec 2019 |
| **Risk Categorisation** | Risk category A according to HRO Art. 7 |
| **Study Design** | Prospective, observational study |
| **Project Design** | A multisite, prospective, observational, study in patients who required a NGT placement.  Group A: etCO2 measurement will be collected 1. after intubation, when the tube is inserted into the endotracheal tube, before proceeding with the aspiration of secretions and 2. once the NGT has been inserted, by a probe located at the end of the tube  Group B: pH measurement will be collected at the end of the procedure, once the NGT is inserted, at 1.a distance of 25 cm from the mouth (esophageal site) and at 2. a distance of 40 cm (gastric site), aspirating the gastric contents and measuring on specific litmus paper.  Group A will be done entirely in the Clinica Luganese Moncucco while group B in the Regional Hospital of Bellinzona. |
| **Background and Rationale** | The laying of a naso-gastric tube (NGT) is an extremely common procedure performed in intensive medicine; although the standard NGT insertion is made at the patient's bed, this procedure is not free of risk. In this setting, can occur serious complications, especially in the sedated, intubated and curarized patient, which does not present the cough reflex. Some studies show an incidence of complications in the NGT pose in around 1% of total insertions, but these complications are associated to a high morbidity, leading to an increase of hospital stay, global mortality and health costs.  Numerous methodologies have been evaluated to recognize the correct positioning of NGT at the gastric level, including different clinical techniques (such as gastric auscultation, aspiration of the NGT), ultrasound techniques, etc. Actually, the diagnostic gold standard is the thoraco-abdominal anterior-posterior radiography, which is considered the only non-invasive method capable to confirm the correct pose of the NGT at intra-diaphragmatic level. This method, however, even if it is non-invasive, requires the use of ionizing radiation (4 uSv for radiography) which could be repeated multiple time for the same patient; NGT may need to be repositioned several times during the same hospital stay, increasing patient exposure to ionizing radiation and, potentially, also the health workers exposure,.  Furthermore, in sedated and intubated patients, the detection cassette is placed under the back. In patients with hemodynamic or respiratory instability, the mobilization required for the detection cassette placement, appears to be a further risk to which the patient could be exposed |
| **Objectives** | To identify into the group A the threshold value between tracheal and esophageal etCO2. To identify into the group B the theshold value between gastric and esophageal pH. |
| **Endpoints** | Group A:  - the aim is to find a threshold value of etCO2 collected when the NGT is well positioned in trachea;  Group B  - the aim is to find a threshold value of pH collected when the NGT is positioned in the esophagus and in the stomach  Secondary endpoints:   - Group A: identify patients suffering from chronic obstructive pulmonary disease (COPD) and perform a sub-analysis to identify the threshold value; - Group B: identify patients taking proton pump inhibitors (PPIs) and perform a sub-anaysis to identify the threshold value in case of an already diagnosed gastro-esophageal reflux disease. |
| **Inclusion- / Exclusion Criteria** | Inclusion criteria:  • Adult patients (> 18 years)  • Patients male and female  • Patients intubated by oro- or naso-tracheal way  • Post-induction curarized patients  • Fasting patients (from at least 6 hours)  Exclusion criteria:  • Patient refusal  • Patients with known bleeding diathesis / ongoing bleeding  • Patients at risk of bleeding (defined as thrombocytes <50 G/l, INR> 2.5, aPTT> 70 sec)  • Patients with traumatic brain injury / Polytrauma  • Patients with esophagus-tracheal fistulas or malformations of the ENT sphere  • Patients with current or previous radiotherapy of the ENT sphere  • Patients unable to give their informed consent due to language barriers  • Women who are pregnant |
| **Procedures and Assessments** | Clinical data will be collected at the NGT positioning |
| **Number of Participants with Rationale** | The study will include a total number of 75 patients (group A: 40 pts, group B: 35 pts) |
| **Study Duration and Schedule** | Planned 01/2020 of First-Participant-In  Planned 01/2021 of Last-Participant-Out |
| **Statistical Considerations** | Sample size: in order to have a significant difference between tracheal and esophageal groups, with a power of 90% and a significance level of 0.01 (one-tailed z test), and anticipating a 10% in the registration failure rate, we plan to enroll 40 patients for group A. In order to have a significant difference between esophageal and gastric pH value, with a power of 90% and a significance level of 0.01 (one-tailed z test), and anticipating a 10% of drop off rate, we plan to enroll 35 patients for group B.  Primary analysis: The adherence to the protocol is checked for each enrolled patient during the study. We assess and report total adherence rate to our protocol in order to analyse data on the intention-to-treat (ITT) and on the per-protocol (PP) population. We test the hypothesis of difference in the proportion of etCO2 level into the tracheal group and into the esophageal group (measurements collect in patients enrolled in group A), with the ITT. We execute a z-test for comparison of the two proportions. The null hypothesis of no difference between the two proportions is not accept if the p-value is 0.01. Similarly, in group B patients is test the hypothesis of difference in the proportion of pH level into the esophageal group and into the gastric group, with the ITT. We carry out a z-test for comparison of the two proportions. The null hypothesis of no difference between the two proportions is not accept if the p-value is 0.01. |
| **Risk / Benefit Assessment** | This study consists in parameters collection in patients who required a NGT positioning. Any potential clinical risk is related only to the standard procedure of NGT placing.  There will be no immediate benefits to the enrolled patients. Future patients who required a NGT positioning could benefit due to the potential of using threshold values as predictors of correct NGT placing, offering better treatment approach which not required thoraco-abdominal anterior-posterior radiography as diagnostic gold standard. |

# BACKGROUND and rationale

## 3.1 Background

The laying of a naso-gastric tube (NGT) is an extremely common procedure performed in intensive medicine; although the standard NGT insertion is performed at the patient's bed, this procedure is not free of risk. In this setting, serious complications can occur, especially in the sedated, intubated and curarized patient, which does not present the cough reflex; for example, complications in the placement of NGT in the lungs could be consequent potential pneumothorax, pneumonia *ab ingestis*, development of a bronco-pleural fistula, alveolar hemorrhages, etc. Some studies show an incidence of complications in the NGT pose in around 1% of total insertions, which are associated to a high morbidity, leading to an increase of hospital stay, global mortality and health costs (1-8, 10-11, 13-14, 16, 19, 21-24, 36, 38, 45, 53-56, 63-65, 67-69).

Numerous methodologies have been evaluated to recognize the correct positioning of NGT at the gastric level, including different clinical techniques (such as gastric auscultation, fluid from the NGT), ultrasound techniques, etc (7, 15, 18, 39-40, 43, 62). Actually, the diagnostic gold standard is the thoraco-abdominal anterior-posterior radiography, which is considered the only non-invasive method capable of confirming the correct NGT pose at intra-diaphragmatic level. However, this non-invasive method requires the use of ionizing radiation (4 uSv for radiography) which could be repeated multiple time for the same patient. As NGT may need to be repositioned several times during the same hospital stay, will be increase ionizing radiation patient exposure. Moreover, there could be an increase to ionizing radiation exposure for health workers too.

Furthermore, in sedated and intubated patients, the detection cassette is placed under the back. As some patients is hemodynamic or respiratory unstable, the required mobilization in order to place the detection cassette in situ, appears to be a further risk.

Many studies has been performed in this field, with the aim to reduce the need of conventional radiography. Chun et al showed how the positioning of the NGT in patients anesthetized, paralyzed and intubated is often difficult due to absence in patient's cooperation; the greater resistance in the NGT passage is localized in the pyriform sinus and in the arytenoid cartilages, which could cause the rolling of the NGT around the oropharynx as already published by Ozer et al. The studied methods resulted ineffective. In the study of Prasad et al the distal tip of the NGT should be lubricated with 2% lidocaine, just as the proximal lumen is filled for 0.5 - 1 cm. When the tip passes the gastresophageal junction and enters into the stomach, there is the formation of a bubble at the distal level due to the presence of gas, the bubble does not form if the NGT is positioned wrongly, or it is repeatedly formed if the NGT is in the trachea. This study, in the current state, does not seem promising(15-16).

Nguyen et al present a case report where it is shown that the use of two-dimensional ultrasound confirms the positioning of the NGT both through the soft tissues of the neck and through the epigastric window; the use of ultrasound at the patient's bed is suggested as a rapid, new and alternative method compared to the radiological "gold standard"(47). Vigneau et al used ultrasound in 35 ICU procedures in adult patients to confirm NGT correct positioning. They demonstrate that the use of ultrasound is faster than radiography and it is sensitive enough confirming 97% of the correct NGT positioning (66). Kim et al published a clinical study designed to compare the effectiveness and limitations of conventional auscultation, pH analysis, radiography and ultrasound; the study Ultrasounds presented a low sensitivity (86%) but high specificity (67%) with a 97% PPV compared to its current gold standard, the chest X-ray; the ultrasound failed to verify gastric positioning in 6 patients (32).

Fernandez et al published a review of diagnostic studies to test pH of aspirate fluids using a litmus paper; in this way they evaluated if the NGT has been placed into the stomach. It has been noted that the color variation could be reduced based on the gastric pH, thus the litmus paper is not considered as sufficiently sensitive (17). A recent clinical trial by Gilbertson et al identified the cut off pH<5.5 to distinguish between the correct positioning in the stomach (20). A study was published by Bercik et al and by Tobin et al in which it was planned to use a magnets to locate and assist the positioning of the SNG (4, 62).

The study documents the accuracy and sensitivity of using a permanent magnet and an external computer to confirm the placement of the NGT in healthy patients. It is an expensive procedure that could not be applied in patients that perform MRI.

It is important to consider that actually the ultrasound methodology results as the most effective procedure, but it presents many limits, between them it requires a specific know how and an ultrasound scanner always available and finally it has a low sensitivity.The medical practice, according to the literature, takes into consideration the following values: etCO2 trachea mean value is 40 mmHg (range 35-45 mmHg) and etCO2 esophagus <25mmHg; pH stomach mean value 3.8 (range 3.2-4.4) and pH esophagus 8.5 (range 6-9.5).

## 3.2 Project rationale and significance

Through the use of methods already adopted in clinical field, we want to collect the values of the etCO2 from the trachea and the pH when the NGT is well positioned in stomach. . There are two methods, already present at clinical level but that need to be implemented: the capnometer and the pH-meter.

The use of the graphic capnometer (capnography) has already been demonstrated to be useful for detecting the positioning of the NGT at the tracheal level (7, 33, 61, 27, 18), even if today there are no studies able to show what is the "threshold level" of the detected CO2 to say with high specificity that NGT is certainly found in the airways (25-27, 31, 33-35, 37, 44, 46, 58-59, 61).

Furthermore, the use of the pH meter has already been remarkably demonstrated to be useful in analyzing the different pH levels in the proximal gastro-enteric tract, with differences between the stomach and the esophagus, even if there are no studies in this sense to identify the "threshold level" below which the pH certainly appears to be a gastric and non-esophageal pH (41-43, 50, 52, 60).

# Study OBJECTIVES and Design

## 4.1 Primary and secondary endpoints

The primary endpoint is to identify the threshold value in the distribution and in the frequency of etCO2 and pH values. The pH values will be compared with the performed X .

The threshold values for etCO2 and for pH will be determined in two groups: group A, with the aim to find a threshold value of etCO2 above which we can be sure that aspiration probe is in the trachea and group B, with the aim to find a threshold value of pH below which we can be certain that NGT is in the stomach.

Further secondary results are expected:

- for patients in group A it will be necessary to perform a sub-analysis for the threshold value in the group of patients suffering from COPD;

- for patients in group B, a sub-group analysis will be performed for the threshold value for patients taking proton pump inhibitors (PPIs), and / or in the presence of an already diagnosed gastro-esophageal reflux disease.

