## 4.3 Study intervention

Group A procedure:

Patients needing the installation of a NGT at the Clinica Luganese Moncucco are consecutively enrolled and selected according to the inclusion and exclusion criteria listed below. The enrolled patients, after receiving adequately protocol study explanation and signed the informed consent, are sedated and intubated according to the clinical indications and the local protocols, independently from the ongoing study.

Anaesthesia is performed by a professional anaesthesiologist and an anaesthetist nurse, using standardized procedures according to local routine protocols. Induction and intubation therefore take place independently of the ongoing clinical study, independent from both indications for intubation, the choice of drugs and intubation material. At the end of the procedure, as usual, the secretions are aspirated with a suction tube of 18 Fr of 6mmdiameter. When the tube is inserted into the endotracheal tube, before proceeding with the aspiration of the secretions, a capnometer is attached to its outer end (picture A), measuring the etCO2 value for 10-15 seconds. At the end of the measurement, we proceed with the aspiration of the secretions as usual.

[figure not shown]
Pic. A

We then proceed with the laying of an NGT according to local protocols. Also in this case, once the NGT has been inserted, the etCO2 is measured at the end of the probe (pic A) for 10-15 seconds and its value is recorded in the CRF. At the end of the measurement, the capnometer can be detached, as a standard procedure, and the NGT can be used as usual.

At the end of the procedure, therefore, for each patient, two values ​​of etCO2 are acquired which will allow to obtain two "populations of values" of the etCO2: the values recorded ​​at the endotracheal level and the one recorded at the esophageal level. Through statistical analysis, we will find the "threshold value" above which the value of etCO2 found is certain for a location in the trachea. The expected mean values of etCO2, according to the literature, are 40 mmHg in the trachea (range 35-45 mmHg) and <25mmHg in the esophagus.

Group B procedure:

The group B enrolment will start at the Regional Hospital of Bellinzona. The enrolled patients are sedated and intubated according to the clinical indications and the local protocols, independently from the ongoing study.

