Anaesthesia is performed by a professional anaesthesiologist and an anaesthetist nurse, using standardized procedures according to local routine protocols. At the end of the procedure, once the NGT is inserted, the pH is measured by aspirating the gastric contents and measuring on specific litmus paper the pH values, both at a distance of 25 cm from the mouth (esophageal site) and at a distance of 40 cm (gastric site).

At the end of the procedure, for each patient two values ​​of pH are acquired which will allow to obtain two pH "value populations": a value at esophageal level and a value at the gastric level. Through statistical analysis (see Section 6), we will try to find the "threshold value" below which the pH is suggestive for a localization in the gastric area.

The expected mean values of pH are 3.8 in the stomach (range 3.2-4.4) and 8.5 in the esophagus (range 6-9.5).

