# STATISTICS AND METHODOLOGY

## 6.1 Determination of sample size

Previous studies allow us to estimate an etCO2 tracheal value of around 40 mmHg (CI 30-50 mmHg). In order to have a significant difference between tracheal and esophageal groups, with a power of 90% and a significance level of 0.01 (one-tailed z test), we calculate a number of 35 patients (57). Anticipating a 10% in the registration failure rate, it appears useful to register at least 40 patients for group A. In the same way we estimate an esophageal pH level value around 7 (CI 5 – 8); in order to have a significant difference between esophageal and gastric pH value, with a power of 90% and a significance level of 0.01 (one-tailed z test), we calculate a number of 30 patients. Anticipating a 10% of drop off rate, it appears useful to register at least 35 patients for each measurement of group B.

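### The primary endpoint is one threshold per marker, but the z-test that Protocol 6.2 names for finding it does not select a cut-off

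*Protocol*

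**What the plan says.** Protocol 4.1 sets the endpoint: "The primary endpoint is to identify the threshold value in the distribution and in the frequency of etCO2 and pH values". It then words the aim in one direction for each marker: an etCO2 value above which the tracheal position is sure, and a pH value below which the gastric position is certain.

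Section 6.2 names the procedure. In each group a z-test compares two proportions, the null hypothesis is rejected at p ≤ 0.01, and this is said to be done in order to identify the threshold. Section 6.2 gives no rule for choosing a cut-off.

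The expected values appear in two sets:

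- Sections 3.1 and 4.3, etCO2: "The expected mean values of etCO2, according to the literature, are 40 mmHg in the trachea (range 35-45 mmHg) and <25mmHg in the esophagus".
- Sections 3.1 and 4.3, pH: "The expected mean values of pH are 3.8 in the stomach (range 3.2-4.4) and 8.5 in the esophagus (range 6-9.5".
- Section 6.1, etCO2: "Previous studies allow us to estimate an etCO2 tracheal value of around 40 mmHg (CI 30-50 mmHg".
- Section 6.1, pH: "we estimate an esophageal pH level value around 7 (CI 5 – 8".

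Section 6.1 does not say whether its CI describes individual readings or a mean.

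**The concern.** A two-proportion test needs a cut-off before there are any proportions to compare. It can show that the two sites differ at that cut-off, but it does not say which cut-off to report. Following 6.2 as written therefore does not produce the endpoint in 4.1.

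The usual repair, a ROC curve with a Youden index, may not help either. In both expected sets the ranges for the two sites do not overlap. If the data look like that, all cut-offs in the gap are equally good by any classification criterion.

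The threshold is the product of the study. Section 3.2 justifies the work by the lack of an etCO2 level that places the tube with high specificity, and section 8.2 foresees such values replacing radiography. A cut-off that can move across a gap by the analyst's choice, with no error rate attached, does not serve that purpose.

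**Working it through.** The protocol states no threshold or selection statistic that could be reproduced. The patient numbers in 6.1 (35 and 30 before losses) are used here only as n. They cannot be re-derived, because 6.1 gives neither proportions nor a standard deviation.

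**1. Gaps between the stated ranges**

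| Source | etCO2, oesophagus / trachea | Gap | pH, stomach / oesophagus | Gap |
|---|---|---|---|---|
| 3.1 and 4.3 | <25 / 35-45 | 25-35 | 3.2-4.4 / 6-9.5 | 4.4-6.0 |
| 6.1 (other site from 4.3) | <25 / 30-50 | 25-30 | 3.2-4.4 / 5-8 | 4.4-5.0 |

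The sets conflict on which cut-offs are safe. With the 6.1 limits taken as hard limits and readings spread evenly, a 35 mmHg cut-off misses (35 − 30)/(50 − 30) = 25% of tracheal readings. A pH cut-off of 6.0 calls (6 − 5)/(8 − 5) = 33% of oesophageal readings gastric.

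**2. The z-test inside the gap**

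z = (p1 − p2) / √[p̄(1 − p̄) · 2/n], where p̄ is the mean of p1 and p2. At any cut-off in the gap p1 = 1, p2 = 0 and p̄ = 0.5.

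- n = 35: z = 1/√(0.25 × 2/35) = 8.37
- n = 30: z = 1/√(0.25 × 2/30) = 7.75

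The value is the same at every cut-off in the gap. Sensitivity and specificity are both 100% throughout, so the Youden index ties as well.

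**3. The z-test outside the gap**

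Inputs: n = 35, trachea uniform on 35-45, oesophagus uniform on 0-25. The uniform shape and the lower limit of 0 are assumptions, since the protocol gives only <25.

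| Cut-off (mmHg) | Tracheal readings above | Oesophageal readings above | z | One-sided p |
|---|---|---|---|---|
| 5 | 1.0 | 0.8 | 2.79 | 0.0026 |
| 20 | 1.0 | 0.2 | 6.83 | <0.0001 |
| 25, 30, 35 | 1.0 | 0.0 | 8.37 | <0.0001 |
| 40 | 0.5 | 0.0 | 4.83 | <0.0001 |
| 43 | 0.2 | 0.0 | 2.79 | 0.0026 |
| 44 | 0.1 | 0.0 | 1.92 | 0.027 |

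Every cut-off checked from 5 to 43 mmHg meets p ≤ 0.01. That includes 5 mmHg, above which 80% of oesophageal readings lie, so significance does not narrow the choice usefully.

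**4. How often the two sites would separate fully**

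This was simulated, with the stated ranges read as about ±2 SD. The answer depends on inputs that the protocol does not give.

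- etCO2, n = 35, oesophagus uniform 0-25 or normal with mean 12.5 and SD 6.25: full separation in 99-100% of runs with tracheal SD 2.5, and in 84-97% with tracheal SD 5.
- Oesophageal mean moved to 20, also below 25, same SD: 71% and 17%.
- Oesophageal mean moved to 24: 23% and 1%.
- pH, n = 30, stomach mean 3.8 and SD 0.3, oesophagus mean 7.75 and SD 0.875: 99.8%.
- The same, but with 20% of patients having gastric pH raised by 1.5 (SD 0.6): about 47%.

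**5. What this number of patients can support**

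With 95% confidence the most extreme of n readings covers at least 0.05^(1/n) of the population:

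- n = 35: 0.05^(1/35) = 0.918, so up to 8.2% may lie beyond it.
- n = 30: 0.05^(1/30) = 0.905, so up to 9.5% may lie beyond it.

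**The case against.** The strongest reply is that full separation is a forecast. Section 4.3 attaches its figures to expected mean values, not to limits on single readings, and for oesophageal etCO2 it gives only an upper bound. The eligibility criteria in 5.1 do not exclude COPD, PPI use or reflux, and 4.1 plans sub-analyses for them. If readings overlap, the data do inform the cut-off and the tie disappears. All of this stands, and step 4 shows how far the result moves. A reader might infer that the tie is nearly certain, or that every value in 25-35 mmHg and pH 4.4-6.0 is bound to separate the sites. The protocol does not support that: the distributions are not given, and 6.1 leaves only the narrower gaps.

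A second reply is that the threshold would not be arbitrary, because the one-directional wording in 4.1 points to the oesophageal edge of any gap. That is also fair: read strictly, it means about 25 mmHg, and about pH 6 (or pH 5 on 6.1). To call the result an arbitrary pick would go too far. But no section turns that wording into a rule, and the test in 6.2 does not implement it.

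A third reply is that a tie rule is detail for a separate analysis plan, and that the protocol proposes neither ROC nor Youden. A missing tie rule alone would indeed be no finding. Here, however, 6.2 names a procedure and states its purpose, and the procedure does not achieve it. ROC and Youden matter only because they are the likely substitutes.

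**Conclusion.** The point holds in a limited form. The procedure in 6.2 does not yield the endpoint in 4.1, and this needs no assumption about separation. If readings do separate as 3.1 and 4.3 expect, an interval up to 10 mmHg or 1.6 pH units wide ties on every classification criterion (5 mmHg or 0.6 units on the 6.1 figures). The probability of that outcome cannot be stated from the protocol. Whether or not the sites overlap, certainty is out of reach: even with no errors, 35 and 30 readings leave upper 95% error limits of 8.2% and 9.5%. These limits assume independent patients who represent those in whom the threshold will be used.

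**What to change.** In 4.1 and 6.2, stop using the z-test as the means of finding the threshold, and define the estimate to match the one-directional aim:

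- **Group A:** the upper one-sided 95%-confidence distribution-free tolerance limit of the oesophageal etCO2 readings.
- **Group B:** the lower one of the oesophageal pH readings.
- **Coverage:** state what is achieved with the number of valid readings. If the extreme reading is used, this is at least 91.8% with 35 patients and 90.5% with 30. Replace the words for certainty in 4.1 by this error bound.
- **Beside the threshold:** report the sensitivity at it, with a confidence interval, and the highest and lowest readings at each site.
- **If there is a gap:** say that the study does not resolve values within it.
- **Expected values:** reconcile 6.1 with 3.1 and 4.3.

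The change takes a few sentences and no new data. The price is a threshold with modest stated coverage instead of one clean number. A limit taken from the extreme reading is also sensitive to a single outlying value, and if the sites overlap it will cost sensitivity, which is why sensitivity must be reported with it.

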## 6.2. Statistical analysis plan

We tabulate the distribution of baseline variables across the study sections, summarizing categorical variables by frequencies and percentage and numerical variables either by mean and standard deviations (±SDs), or by medians and interquartile ranges (IQR). Data distribution was verified using a Kolmogorov- Smirnov test.

We checked adherence to the protocol for each patient during the study. We assess and report total adherence rate to our protocol in order to analyse data on the intention-to-treat (ITT) and on the per-protocol (PP) population. Primary analysis is carried out on the ITT population for each study group, irrespective of potential non-adherence to the study protocol. Secondary analyses included analysis on the PP population, concerning the patients enrolled and treated following all the study procedures. The results of the performed analyses on the two populations are compared. All hypothesis tests are one-sided and considered significant if p-value is ≤ 0.01. Analyses are accomplished with the intention-to-treat if not otherwise specified.

In group A we tested the hypothesis of difference in the proportion of etCO2 level into the tracheal group and into the esophageal group (measurements collected in patients enrolled in group A), with the ITT. We executed a z-test for comparison of the two proportions, refusing the null hypothesis of no difference between the two if the p-value was ≤0.01. This to identify the threshold value of etCO2 above which tracheal location of NGT is determined with high precision. Similarly, in group B we tested the hypothesis of difference in the proportion of pH level into the esophageal and gastric group, with the ITT. We carried out a z-test for comparison of the two proportions, refusing the null hypothesis of no difference between the two if the p-value was ≤ 0.01. This to identify the threshold value of pH below which gastric location of NGT is determined with high precision. Statistical analysis was performed using SPSS version 10.0 (IBM, Chicago, IL, USA) for Mac OS.

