## 8.2 Risk-benefit assessment

This study consists in several parameters collection in patients who required a NGT positioning. Thus, any potential clinical risk is related only to the standard procedure of NGT placing.

There will be no immediate benefits to the enrolled patients. Future patients who required a NGT positioning could benefit due to the potential of using threshold values as predictors of correct NGT placing, offering better treatment approach which not required thoracic-abdominal anterior-posterior radiography as diagnostic gold standard.

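### Group A defines only an etCO2 cut-off that rules the trachea in; confirming correct placement without X-ray also needs one that rules the trachea out

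*Protocol*

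**What the plan says.** The direction of the group A cut-off is the same wherever the protocol gives one.

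- Section 3.2 names the missing knowledge as a CO2 level "to say with high specificity that NGT is certainly found in the airways".
- Section 4.1 makes the endpoint a "threshold value of etCO2 above which we can be sure that aspiration probe is in the trachea".
- Section 4.3 looks for the value "above which the value of etCO2 found is certain for a location in the trachea".
- Section 6.2 gives the purpose of the test: "This to identify the threshold value of etCO2 above which tracheal location of NGT is determined with high precision".

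The synopsis objective speaks only of a value between the two sites and gives no direction.

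The intended use is stated elsewhere. The study title describes the "measurements as markers to confirm during the correct naso-gastric tube placement in unconscious patients". Section 8.2, and the matching synopsis row, see a future benefit in the "potential of using threshold values as predictors of correct NGT placing, offering better treatment approach which not required thoracic-abdominal anterior-posterior radiography".

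For group B, section 4.1 seeks a "threshold value of pH below which we can be certain that NGT is in the stomach". Sections 4.2 and 4.3 provide for pH readings from the oesophagus and the stomach only.

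**The concern.** A cut-off chosen so that readings above it are surely tracheal is governed by the upper tail of the oesophageal readings. It limits how often a tube in the oesophagus is mistaken for one in the airway. It says nothing direct about a reading below it, and that is the reading a user would take as reassurance.

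Treating a low reading as evidence against airway placement relies on the lower tail of the tracheal readings. The error that counts for this use is an airway placement that reads low and is accepted. Section 3.1 describes the harm: lung complications in curarized patients who have no cough reflex. No section sets a value below which the trachea is excluded, and none sets a target for sensitivity. The endpoint could therefore be met as written while the property behind the claimed benefit was never estimated.

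**Working it through.** **No stated figure to reproduce.** The point concerns direction, and no figure in the plan bears on it. The number of evaluable pairs follows from 6.1: 35 calculated, 40 enrolled with 10% registration failure, and 40 × 0.9 = 36. So there are about 35-36 pairs.

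**Inputs from the protocol.** Tracheal etCO2 has mean 40 mmHg, with range 35-45 (3.1, 4.3) and an interval of 30-50 (6.1). The oesophageal value is below 25 mmHg (3.1, 4.3). No standard deviation is given.

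**Assumptions.** Readings are normal. Reading each tracheal interval as a 95% range gives SD = 10/3.92 = 2.55 or 20/3.92 = 5.10. The oesophageal mean is taken as 10-20 and the SD as 5-6; these values are not in the protocol.

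**Step 1: the protocol's ranges taken literally.** With trachea at 35-45 and oesophagus below 25, any cut-off from 25 to 35 separates the sites in both directions. The mismatch then has no numerical effect.

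**Step 2: tracheal readings below a given cut-off c.** Share = Φ((c − 40)/SD).

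| c (mmHg) | SD 2.55 | SD 5.10 |
|---|---|---|
| 25 | Φ(−5.88) ≈ 0% | Φ(−2.94) = 0.2% |
| 30 | Φ(−3.92) < 0.01% | Φ(−1.96) = 2.5% |
| 35 | Φ(−1.96) = 2.5% | Φ(−0.98) = 16% |

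**Step 3: where a rule-in cut-off would fall.** Take it as the highest of 36 simulated oesophageal readings, so that no observed oesophageal value exceeds it. The misses are averaged over the simulated cut-offs.

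| Oesophageal mean, SD | Average cut-off (mmHg) | Tracheal readings below it (SD 2.55 to 5.10) |
|---|---|---|
| 10, 5 | 20.6 | under 0.1% |
| 15, 6 | 27.7 | 0.2% to 2.0% |
| 20, 5 | 30.6 | 0.6% to 4.9% |
| 20, 6 | 32.7 | 3.6% to about 10.8% |

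Across the grid the cut-off averages about 20.6-32.7 mmHg, and misses run from about 0 to 11%.

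**Step 4: the two cut-offs can differ.** With trachea N(40, 5.1) and oesophagus N(20, 5), the 99%-specificity cut-off is 31.6 mmHg and 5.0% of tracheal readings lie below it. The 99%-sensitivity cut-off is 28.1 mmHg.

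**Step 5: what the sample can show.** With zero misses among n tracheal readings, the exact one-sided 95% lower bound on sensitivity is 0.05^(1/n). This is 91.8% for n = 35 and 92.0% for n = 36. With zero misses, a bound of 95% needs ln 0.05/ln 0.95 = 58.4, so 59 readings; 98% needs 149 and 99% needs 299.

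**The case against.** The best defence is that the endpoint matches its own rationale. Section 3.2 asks for specificity for the airway, and 4.1, 4.3 and 6.2 follow it. Detecting misplacement is a legitimate aim. Section 8.2 speaks of potential future benefit, and 4.2 says care does not depart from standard, so no participant is managed by the cut-off. Both sets of readings are collected, so both tails could be reported. All of this stands. It makes the endpoint coherent for detecting misplacement, but it does not supply what the title and 8.2 need, and the direction of a primary endpoint is fixed in the protocol rather than left to an analysis plan.

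The numerical objection also stands in part. On the expected ranges one cut-off does both jobs, and the larger misses come from assumed oesophageal means near 20, where 16-20% of oesophageal readings would exceed 25 mmHg, against the protocol's expectation if that is read as a limit. However, 4.3 lists the oesophageal figure among mean values, 6.1 uses the wider 30-50 interval, and a COPD sub-analysis is planned, so clean separation cannot be taken for granted.

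A reader might infer that the dangerous error is uncontrolled whatever the data show. The documents do not support that, because with clean separation it is controlled incidentally. Nor does the 92% bound show that the direction is wrong: it reflects sample size and applies equally to a rule-out cut-off.

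On group B, the synopsis and 3.2 already frame the question as gastric versus oesophageal, and 4.3 says only that a low pH is suggestive. The overreach is confined to the certainty claimed in 4.1.

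**Conclusion.** The point holds as a mismatch between the group A endpoint and the stated use. The plan targets specificity for the trachea; confirmation of placement without X-ray also requires sensitivity for the trachea, which is nowhere targeted. The consequence is conditional. It is nil if the readings separate as section 3.1 expects. If they overlap, about 0-11% of tracheal readings fall below the rule-in cut-off, given normal readings, tracheal mean 40 with SD 2.55-5.1, and an assumed oesophageal mean of 10-20 with SD 5-6.

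Separately from direction, about 35-36 pairs cannot demonstrate more than about 92% sensitivity even with no misses. Excluding the trachea would also not distinguish oesophagus from stomach; group B studies that in other patients, without airway pH. X-ray replacement therefore cannot be concluded from this study alone, under either cut-off.

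**What to change.** Choose one of two routes.

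1. **Add the second cut-off.** In 4.1 and 6.2, define from the same paired readings a rule-out etCO2 cut-off at a pre-stated sensitivity for the trachea, alongside the rule-in cut-off. Report sensitivity and specificity with exact confidence bounds at each. Base any statement about excluding airway placement on the rule-out cut-off.
2. **Narrow the claim.** Restrict the title, synopsis and 8.2 to detection of airway misplacement.

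Under either route:

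- State that about 35-36 evaluable pairs with zero misses support only about 92% sensitivity (one-sided 95% bound), and that replacement of X-ray is not a conclusion of this study alone.
- Reword the group B aim in 4.1 as gastric rather than oesophageal, in line with the synopsis objective and 3.2.

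Cost: no change to procedures or enrolment. Route 1 needs a small added analysis, since 6.2 plans only a z-test of two proportions and no procedure that would yield a second cut-off. The downside of both routes is a narrower claim; demonstrating higher sensitivity would need the larger numbers shown above.
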